## Abstract

**Background:**

Ankle-foot orthoses (AFOs) are vital in gait rehabilitation for patients with stroke. However, many conventional AFO designs may not offer the required precision for optimized patient outcomes. With the advent of 3D scanning and printing technology, there is potential for more individualized AFO solutions, aiming to enhance the rehabilitative process.

**Objective:**

This nonrandomized trial seeks to introduce and validate a novel system for AFO design tailored to patients with stroke. By leveraging the capabilities of 3D scanning and bespoke software solutions, the aim is to produce orthoses that might surpass conventional designs in terms of biomechanical effectiveness and patient satisfaction.

**Methods:**

A distinctive 3D scanner, complemented by specialized software, will be developed to accurately capture the biomechanical data of leg movements during gait in patients with stroke. The acquired data will subsequently guide the creation of patient-specific AFO designs. These personalized orthoses will be provided to participants, and their efficacy will be compared with traditional AFO models. The qualitative dimensions of this experience will be evaluated using the Quebec User Evaluation of Satisfaction With Assistive Technology (QUEST) assessment tool. Feedback from health care professionals and the participants will be considered throughout the trial to ensure a rounded understanding of the system’s implications.

**Results:**

Spatial-temporal parameters will be statistically compared using paired *t* tests to determine significant differences between walking with the personalized orthosis, the existing orthosis, and barefoot conditions. Significant differences will be identified based on *P* values, with *P*<.05 indicating statistical significance. The Statistical Parametric Mapping method will be applied to graphically compare kinematic and kinetic data across the entire gait cycle. QUEST responses will undergo statistical analysis to evaluate patient satisfaction, with scores ranging from 1 (not satisfied) to 5 (very satisfied). Satisfaction scores will be presented as mean and SD values. Significant variations in satisfaction levels between the personalized and existing orthosis will be assessed using a Wilcoxon signed rank test. The anticipation is that the AFOs crafted through this innovative system will either match or outperform existing orthoses in use, with higher patient satisfaction rates.

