#### Clinical Outcomes

In the pursuit of developing an optimized orthotic design system, an array of clinical metrics is implemented to gauge its efficiency, efficacy, and the comfort it bestows on both patients and health care professionals. Ensuring a comfortable experience for the patient during the photography process is paramount, given its pivotal role in orthotic design. This precision not only benefits the patient but also ensures that the system health care professionals navigate is intuitive.

Biomechanical assessments use the Qualisys Miqus M3 system, paired with Bertec force platforms. Patients will wear the Calibrated Anatomical System Technique lower body marker set, which consists of 36 reflective markers, as prescribed by Cappozzo et al [20]. Observations cover 3 walking conditions for each participant: unaided (where possible), with the current orthosis, and with the newly designed orthosis. This methodology provides an in-depth understanding of the orthosis’s efficacy, drawing from 10 walking cycles for each leg, and analyzing both kinematics and kinetics.

The biomechanical data under scrutiny spans temporal-spatial parameters, which capture walking speed, gait cycle duration, step length, step time, time in stance, and time in swing. Kinematic parameters delve into pelvic movements such as anterior tilt, up obliquity, and internal rotation. Hip parameters include flexion, adduction, and internal rotation, while knee parameters assess flexion, varus, and internal rotation. Ankle and foot evaluations note dorsiflexion, inversion, pitch, and internal progression. Kinetic parameters are marked by the internal moments at the hip (extensor and valgus), knee (extensor and valgus), and ankle (plantarflexor and extensor), accompanied by the vertical ground reaction force.

The qualitative patient analysis will also incorporate the QUEST assessment. QUEST focuses on understanding the user’s satisfaction with assistive technology. It evaluates a range of aspects, from device functionality to user confidence. This offers insights into patients’ perceptions and benefits derived from the new orthosis in comparison to conventional models. Incorporating QUEST ensures the orthosis not only meets clinical requirements but also aligns with patient preferences and comfort levels.

Through these comprehensive evaluations, the study aims to offer an enriched perspective on the potential and effectiveness of the innovative orthotic system.

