### Data Analysis

The forthcoming data analysis is designed to provide an in-depth understanding of the impact of personalized orthoses on gait parameters in relation to both preexisting orthosis and barefoot walking. The sample size was estimated at a prespecified power of 90%, while the α value was set at <.05. The primary outcomes will be represented through spatial-temporal data tables and normalized gait graphs, spanning from 0% to 100% of the gait cycle for the left and right legs.

Spatial-temporal parameters will undergo statistical comparisons using paired *t* tests. This will discern any significant differences between walking with the personalized orthosis, the preexisting orthosis, and walking barefoot. Significant distinctions will be recognized based on *P* values, with a threshold set at 95% indicating statistical significance.

Graphical comparisons of kinematic and kinetic data will use the Statistical Parametric Mapping (SPM) method. SPM is tailored for the analysis of 1D biomechanical data series, such as kinematic curves, yielding a nuanced understanding of differences across the entire gait cycle rather than mere isolated time points. The analysis will leverage the *SPM1D* script. By using SPM1D, it becomes feasible to pinpoint regions in the gait cycle where palpable differences between conditions (existing orthosis, personalized orthosis, and barefoot) arise. This rigorous method offers a continuous evaluation over the entire time or space continuum, safeguarding against missing subtle yet clinically pivotal variations.

Simultaneously, the QUEST responses will be statistically analyzed to evaluate patient satisfaction. Scores from the QUEST, which range from 1 (not satisfied) to 5 (very satisfied), will be presented as mean and SD values for each question. A 1-sample *t* test will be used to determine if the mean satisfaction scores significantly differ from a neutral value. Additionally, a Wilcoxon signed rank test may be used to determine differences in satisfaction levels between using the personalized orthosis and the preexisting orthosis. Any statistically significant variations in user satisfaction between the 2 orthoses will provide insight into the preferential use and comfort of the personalized design.

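### Testing vertical ground reaction force by SPM over the whole gait cycle leaves swing with no defined test and can show a stance-timing change as a loading difference

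*Protocol article*

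**What the plan says.** Data Analysis assigns the method without separating kinetics from kinematics: "Graphical comparisons of kinematic and kinetic data will use the Statistical Parametric Mapping (SPM) method". It describes the method as "yielding a nuanced understanding of differences across the entire gait cycle rather than mere isolated time points", and the curves are to be shown as "normalized gait graphs, spanning from 0% to 100% of the gait cycle for the left and right legs". The abstract repeats the whole-cycle comparison explicitly for kinetic data: "The Statistical Parametric Mapping method will be applied to graphically compare kinematic and kinetic data across the entire gait cycle".

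Clinical Outcomes lists the kinetic data as internal moments at the hip, knee and ankle, "accompanied by the vertical ground reaction force". The same section lists the temporal-spatial parameters: "walking speed, gait cycle duration, step length, step time, time in stance, and time in swing". Data Analysis compares these between conditions by paired t test. The purpose given for SPM1D is to locate the regions of the cycle where "differences between conditions (existing orthosis, personalized orthosis, and barefoot) arise".

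The article nowhere limits the force curve to stance, aligns curves at toe-off, or says how the zero-force part of the cycle is handled.

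**The concern.** Vertical ground reaction force exists only while the foot is on the plate. Putting it on a 0-100% gait-cycle axis has two effects.

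- **Undefined segment.** Once every participant has left the plate in both conditions, all paired differences are exactly zero and no t value exists. Masking or trimming that segment changes the length of the searched interval, and with it the threshold for the rest of the curve. That choice is better fixed before the data are seen.
- **Timing shown as loading.** If stance takes a larger share of the cycle in one condition, that condition still carries load at points where the other shows none. SPM can flag this region although loading within stance is the same.

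At stake is interpretation. The location of a flagged region is the result SPM is meant to deliver, so a timing change could be reported as the personalized orthosis altering limb loading.

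**Working it through.** **Plan's own figure.** There is none to reproduce: the article gives 90% power and an α of .05 but no n, SD or stance share. Every numerical input below is an assumption.

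**1. Undefined nodes.** The paired statistic at node q is t(q) = mean D(q) / (sd D(q) / √n), where D is the within-patient force difference. If both forces are zero in every patient, D(q) = 0 for all and t(q) = 0/0.

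Paired curves were simulated on 101 nodes with mean stance 64% of the cycle, between-patient SD 3 points and within-person SD 1 point. The first undefined swing node fell on average at 70.0 (n=10, no shift) to 74.6 (n=20, 4-point shift). That leaves 101 − 70.0 = 31.0 to 101 − 74.6 = 26.4 swing nodes. Adding the zero at initial contact gives the simulated totals of 32.0 and 27.4. A second set of assumptions (stance 66%, SD 4) gave 25-29.

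**2. Why a timing shift registers.** Let stance share s = stance time / cycle time, δ the mean shift in s between conditions, and σ the within-person noise in s per condition. Near toe-off the force falls with slope g, so D(q) ≈ g(δ + error), and the error has SD σ√2. The slope cancels: t ≈ δ / (σ√2/√n). For δ = 2 points:

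| σ (points) | n=10 | n=20 |
|---|---|---|
| 1 | 4.47 | 6.32 |
| 2 | 2.24 | 3.16 |
| 3 | 1.49 | 2.11 |

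The random-field 5% thresholds in the simulated curves were about 4.8 (n=10) and 3.8 (n=20). This first-order ratio ignores spread in toe-off between patients. It shows why within-person noise governs the size. If stance and cycle time change by the same factor, s is unchanged, δ = 0, and there is no artefact.

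**3. Simulated rate of a flagged force difference, same mean loading within stance.** Threshold: 5% family-wise max-|t| by sign-flipping, as a stand-in for the random-field threshold.

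| Shift in stance share | σ | n=10 | n=20 |
|---|---|---|---|
| 0 | 1 | 4.7% | 4.7% |
| 2 points | 1 | 81% | 100% |
| 2 points | 2 | 36% | 66% |
| 2 points | 3 | 14% | 41% |

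The threshold method matters too. With a random-field threshold, σ = 1, stance 66% (SD 4) and a 2-point shift, the rates were 53% (n=10) and 98% (n=20), against 1-2% with no shift. The sign-flip rates may therefore be on the high side for a random-field analysis.

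**4. After the fix.** With the force curve on 0-100% of stance and a 4-point shift in stance share, the rate was 5.7% (n=10) and 6.0% (n=20). Over 300 replicates the Monte Carlo standard error is √(0.05 × 0.95 / 300) = 1.3 points, so both agree with 5%. Only the two end points were undefined, being zero by construction.

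**The case against.** **The wording may be general.** The 0-100% phrase describes how outcomes are displayed, the whole-cycle phrase contrasts SPM with single time points, and a stance window for one channel is a detail that a condensed article may leave to a fuller plan. The display point is fair. But the abstract applies the whole-cycle comparison to kinetic data by name, and a stance window for force would depart from it. This is a stated domain and not an omission.

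**Undefined nodes do no inferential harm by themselves.** This stands. A reader might infer that the 0/0 segment produces false findings. It cannot, because nothing there can cross a threshold. It only forces an unplanned decision about the search interval.

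**The force really does differ at that percentage of the cycle.** This also stands. The flagged region is a true difference on the cycle axis, and the risk is attributing timing to loading. Cycle-normalised joint curves share some of this timing effect.

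**The timing change is visible elsewhere.** Stance time and cycle duration are both listed, and the article sets no decision rule on vertical force. A reader would usually see the timing change beside the flagged region. This reduces the harm but does not say which part of the force result is timing.

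**Ankle moments.** A reader might extend the 0/0 problem to them. The article gives no basis for that: joint moments are generally non-zero in swing, so whole-cycle SPM can be computed for them.

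**Conclusion.** The point holds for vertical ground reaction force, one of about 20 curves listed (13 kinematic, 7 kinetic). Followed as written, the plan leaves about a quarter of that curve's axis without a defined test, assuming stance near 65% of the cycle. It also lets a change in stance share appear as a force difference around toe-off.

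The direction follows from arithmetic; the size does not come from the document. For a 2-point shift the simulated rate spans 14-81% at n=10 and 41-100% at n=20, as within-person stance noise falls from 3 points to 1. It is nominal when stance share does not change. No single figure in those ranges is a property of this trial.

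Two stronger conclusions a reader might draw are not supported: that the kinetic result would be wrong outright, and that the effect would be formally counted twice. The article does not combine outcomes into a count, and the flagged difference is real on its own axis. The supported conclusion is that it may be misattributed. The change is worth making because the remedy is specific and nearly free.

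**What to change.** In Data Analysis, and in the matching sentence of the abstract, state that vertical ground reaction force is time-normalised to 0-100% of stance (foot contact to toe-off), that SPM for this curve is run on that interval only, and that stance-duration effects are reported through the existing time-in-stance parameter. Keep the whole gait cycle for joint angles and joint moments.

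The cost is a sentence and a processing setting. Foot contact and toe-off must already be identified to obtain stance and swing times, so no new data are needed. The one drawback is that the force curve will have a different x-axis from the other curves.

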**Conclusions:**

Embracing the synergy of technology and biomechanics may hold the key to revolutionizing orthotic design, with the potential to set new standards in patient-centered orthotic solutions. However, as with all innovations, a balanced approach, considering both the technological possibilities and individual patient needs, will be paramount to achieving optimal outcomes.

**International Registered Report Identifier (IRRID):**

PRR1-10.2196/52365

## Introduction

### Overview

Stroke, often termed a cerebrovascular accident, poses a monumental global health issue and stands as the second leading cause of mortality worldwide [1]. In addition to the grave concern of mortality, survivors of stroke frequently grapple with substantial morbidity, most notably neurological impairments that substantially hamper their quality of life. Among these impairments, a prevalent issue is equinovarus foot, a symptom characterized by the foot being plantarflexed (downward) and inverted (turned inward), often resulting from muscle imbalances or neurological impairments [2,3]

In the management and rehabilitation of the equinovarus foot, ankle-foot orthoses (AFOs) serve as a foundational element, supporting and aligning the ankle and foot, suppressing spastic and overpowering muscles, and assisting weak or paralyzed muscles [4]. While these devices are indispensable in aiding patients to regain some semblance of normal gait, they come with their own sets of limitations. Broadly speaking, AFOs are categorized into 2 primary types: traditional off-the-shelf models and custom-crafted versions. Traditional AFOs, designed for a broad patient demographic, offer widespread accessibility but often miss the mark in addressing the unique biomechanical needs of each patient. This one-size-fits-all approach has drawn criticism for its rigidity and lack of individual customization [5]. Conversely, custom-made AFOs are meticulously tailored to fit a specific patient’s anatomical structure. While they provide a more individualized fit, the process of creating these orthoses is time-consuming and very laborious. In addition, the process is also wasteful of materials, as plaster molds and other excess fabrication materials are discarded during the fabrication process [6]. This gap between age-old craftsmanship and cutting-edge precision sets the stage for technological intervention, aiming to meld the advantages of both approaches.

The concept of reverse engineering in orthotics involves capturing a patient’s limb anatomy in great detail, translating this information into a digital model, and then crafting an orthotic device to perfectly align with the individual’s biomechanical demands [7,8]. Using 3D scanning techniques allows for a highly accurate representation of human anatomy. This digital replica serves as a blueprint upon which orthotic devices can be meticulously designed, thereby ensuring that the device is tailored to an individual’s unique biomechanical requirements. Nevertheless, the integration of 3D scanning technology into the orthotic field is fraught with challenges. Capturing a comprehensive scan, particularly of the plantar region of the foot, proves to be problematic. The quality of the scan is often compromised due to patient movements, exacerbated by the extended duration needed for the scanning process [9]. This prolonged duration can be uncomfortable for the patient, thereby leading to unintended movements and consequential errors in the scan data. Moreover, there are ongoing debates over the computational workload and adaptability of the resulting digital models. Such pitfalls, whether arising from anatomical complexities, patient movements, or technological limitations, could culminate in an improperly fitting orthotic device.

The science of photogrammetry, which involves making measurements based on photographs, offers a potential solution. Initially used for mapping and topographical studies [10], its application in the medical realm, particularly in orthotics and prosthetics, has only recently been explored. The capacity to transform photographs into intricate 3D models offers quicker scan times and could minimize errors induced by patient movements [11]. However, the full-scale integration of this promising technology into the orthopedic field is still in its infancy [12-16]. Ensuring that the resulting 3D models are an accurate reflection of patient anatomy and that the resultant devices are both functional and comfortable remains a challenge. Furthermore, orthopedics is a multidisciplinary field that includes physicians, physical therapists, and engineers. Consequently, any new technological adoption must be orchestrated carefully to ensure effective use across all these professions [17]. Armed with these technological advancements, the field of orthotics is poised for a transformative evolution—a shift toward a more patient-centric and technologically integrated paradigm. This fusion of traditional orthotic craftsmanship with cutting-edge computational tools heralds a new era in patient care, targeting both precision and broad accessibility.

### Goal of This Study

This research protocol delineates our approach to developing a next-generation AFO system tailored to meet the specific needs of survivors of stroke. The primary objective is to harness advanced scanning tools and bespoke software for a holistic orthotic solution. By innovatively integrating technology and medical expertise, we envision a transformation in the rehabilitation journey, creating a more refined and effective recovery pathway for individuals with poststroke motor challenges. Our methodological framework will guide us from the initial stages of scanner and software development to a culminating phase of validation, where the proposed orthotic devices will undergo rigorous patient trials. Through this initiative, we aim to chart a progressive path in the realm of poststroke orthotic care.

## Methods

### Study Design

This nonrandomized feasibility study aims to harness advanced scanning technologies and innovative software for the design and refinement of orthotics tailored specifically to the unique anatomical and biomechanical needs of survivors of stroke presenting with equinovarus deformity. Following a noninferiority trial design for biomechanical outcomes and a superiority trial design for qualitative outcomes, our methodology focuses on the development of a novel AFO system. The goal is to ensure its biomechanical performance is at least as effective as off-the-shelf AFOs while also enhancing patient satisfaction. Feedback from patients and clinical observations will serve as the primary indicators of success.

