## Results

The methodology and approach of this research harbor specific expectations concerning its outcomes. We will use the Qualisys Track Manager from Qualisys to capture biomechanical data with unparalleled accuracy. Once gathered, the data will be processed and analyzed rigorously. With the integration of the Project Automation Framework from Qualisys and Visual 3D from C-Motion, the raw biomechanical data will be transformed into actionable insights that promise to inform and refine orthotic design.

One of the primary quantitative expectations is that the orthosis developed through the new system will either match or surpass the performance of the patient’s current orthosis. This benchmark stems from the belief that the integration of state-of-the-art technology and personalized biomechanical data can achieve superior orthotic design. On the qualitative front, using the QUEST assessment, the expectation leans toward higher satisfaction rates with the new orthosis. Since the orthosis is tailored specifically to the patient’s leg, it is anticipated that its unique design will resonate more with patients, ensuring better fit, comfort, and overall user experience. To ensure comprehensive results, feedback from health care professionals and participants will be actively sought throughout the trial phases. This blend of qualitative and quantitative data aims to present a holistic perspective on the impact of the new orthotic design, setting the stage for potential breakthroughs in patient-centered orthotic solutions. In summary, while this research protocol lays out the groundwork and anticipated outcomes, the subsequent study will seek to not just present numbers but to demonstrate the tangible and intangible benefits of a personalized orthotic approach.

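### Noninferiority is declared for the biomechanical outcomes, but the only analyses fixed for them are tests of difference, which cannot establish it

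*Protocol article*

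**What the plan says.** The Study Design section of the protocol article states the design as "Following a noninferiority trial design for biomechanical outcomes and a superiority trial design for qualitative outcomes". It gives the purpose as follows: "The goal is to ensure its biomechanical performance is at least as effective as off-the-shelf AFOs while also enhancing patient satisfaction".

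The Data Analysis section then fixes the biomechanical analysis:

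- For the spatial-temporal variables: "Spatial-temporal parameters will undergo statistical comparisons using paired *t* tests". The stated purpose is: "This will discern any significant differences between walking with the personalized orthosis, the preexisting orthosis, and walking barefoot".
- For the kinematic and kinetic curves, SPM1D is used because "it becomes feasible to pinpoint regions in the gait cycle where palpable differences between conditions (existing orthosis, personalized orthosis, and barefoot) arise".
- Findings are recognised from P values. The abstract says "Significant differences will be identified based on" P values, with P<.05 as the threshold.

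The one-sample t test and the Wilcoxon signed rank test concern only the satisfaction questionnaire (QUEST), which belongs to the superiority part of the design.

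The Results section expects that the new orthosis "will either match or surpass the performance of the" patient's current orthosis, and the abstract says much the same. The Data Analysis section reports 90% power at an α of .05. The article does not give a number of participants, an effect size, an SD, a margin or the hypothesis to which that power refers.

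**The concern.** Noninferiority and difference testing have different null hypotheses. A noninferiority analysis starts from the position that the new device is worse by at least a margin, and asks whether the data rule that out. A test of difference starts from equality and asks whether the data rule that out. Failing to reject equality leaves the noninferiority question open.

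Under the plan as written, only a significant advantage for the new orthosis could support the expected conclusion. The lesser claim, that it matches the existing device, has no valid route. If nonsignificance were used for that purpose, an orthosis worse by a clinically relevant amount could pass, and a larger SD or smaller sample would make this more likely. Conversely, a precise study could find a significant deficit that lies well inside any sensible margin, and the plan has no rule to say that this is still acceptable.

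**Working it through.** **1. The plan's own figure.** The 90% power cannot be reproduced, because the article gives no sample size, effect, SD or margin. What follows uses assumed values and illustrates the size only.

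**2. The two rules side by side.** Let D be the mean paired difference in walking speed (personalized minus existing orthosis), s the SD of the paired differences, n the number of participants and M the margin.

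- Rule in the article: compare |D|/(s/√n) with the t critical value t(0.975, n−1). The article does not state sidedness. I take the test as two-sided because it looks for any difference.
- Noninferiority rule: conclude noninferiority if D − t(0.975, n−1)·s/√n > −M.

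Two worked cases, with M = 0.10 m/s assumed, show that the rules can disagree in both directions:

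- n=20, s=0.20, observed D=−0.05. Half-width = 2.093 × 0.20/√20 = 0.094. The 95% CI is −0.144 to +0.044. The difference is not significant, yet a deficit larger than the margin is not excluded.
- n=30, s=0.10, observed D=−0.04. Half-width = 2.045 × 0.10/√30 = 0.037. The 95% CI is −0.077 to −0.003. The deficit is significant, yet noninferiority is shown.

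**3. How often a device worse by the full margin is not found significantly worse.** Assumed: true difference −0.10 m/s, equal to the margin, and s of 0.10, 0.15 or 0.20 m/s. The test statistic follows a noncentral t distribution with n−1 degrees of freedom and noncentrality −(0.10/s)·√n. The probability wanted is 1 − P(T < −t(0.975, n−1)). For n=20 and s=0.20 the noncentrality is −0.5 × √20 = −2.236, the critical value is 2.093 and the result is 43.6%.

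| n | s=0.10 | s=0.15 | s=0.20 |
|---|---|---|---|
| 10 | 19.7% | 53.1% | 70.7% |
| 15 | 5.1% | 32.9% | 56.2% |
| 20 | 1.1% | 19.3% | 43.6% |
| 30 | 0.04% | 5.8% | 24.6% |

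The noninferiority rule passes the same device in 2.5% of trials in every cell, by construction. The low values at s=0.10 do not make the difference test valid. Its error at the margin is simply not controlled and moves with n and s.

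**4. If the 90% power refers to the margin.** The chance of missing a deficit of exactly that size is then 100% − 90% = 10%, four times 2.5%. As a check, with a margin of 0.5 SD, 90% power needs 44 pairs, and at n=44 the chance of a nonsignificant result is 10.0%.

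**5. What a noninferiority test would need.** For 90% power with a true difference of zero and one-sided α of .025, the pairs required are 265, 119, 44, 19 and 13 for margins of 0.2, 0.3, 0.5, 0.8 and 1.0 SD of the paired difference.

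**The case against.** **Low power.** A reader might infer that the study is underpowered. The article does not support that. It states 90% power and gives no sample size, so low power can be neither shown nor ruled out. The flaw does not depend on it.

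**Nonsignificance read as matching.** The article nowhere says that it will read a nonsignificant result this way. The statements about matching or exceeding the current orthosis are expectations, not decision rules. This stands as a limit on what can be claimed. It remains true that the article gives no other rule for reaching the conclusion it expects.

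**Superiority wording.** The abstract's Objective says "the aim is to produce orthoses that might surpass conventional designs in terms of biomechanical effectiveness and patient satisfaction", which might be read as a contradiction of the noninferiority design. It is aspirational wording, and it is compatible with testing noninferiority first and superiority afterwards.

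**Detail left elsewhere.** A margin value, a direction of benefit for each variable and the choice of one lead variable may be in a full protocol or analysis plan that is not shown. Their absence alone is no finding. The conflict is different in kind: the article itself names the tests, their purpose and the threshold, and these do not fit the design it declares. An analysis plan that follows the article inherits the problem, and one that uses a margin departs from the article.

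**Feasibility study.** The study is labelled a feasibility study and names patient feedback and clinical observations as its main signs of success. This lessens the weight of any single biomechanical conclusion. It does not remove the conflict, because the same section declares noninferiority and the Data Analysis section treats the gait tables and graphs as primary outcomes.

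**Conclusion.** The point holds. The article declares noninferiority for the biomechanical outcomes and fixes only tests of difference for them, so the stated analysis cannot establish the stated objective, whatever the power.

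The size cannot be taken from the article. Under the assumed 0.10 m/s margin and SD range of 0.10 to 0.20 m/s, the chance that a device worse by the full margin is not found significantly worse runs from 0.04% (n=30, smallest SD) to 71% (n=10, largest SD). The margin-based rule gives a fixed 2.5%. In some cells the difference test is stricter than 2.5%, so the fault is lack of control and not always leniency. These figures depend on the assumed margin, SDs and sample sizes, approximately normal paired differences and a two-sided test. The conflict between design and analysis depends on none of them.

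**What to change.** Choose one spatial-temporal variable with a clear direction of benefit, for example walking speed, personalized minus existing orthosis. State a clinically justified margin in advance. Conclude noninferiority only if the lower limit of the two-sided 95% CI for the mean paired difference lies above minus that margin, and test superiority only after that. State that the 90% power refers to this test, with the margin, SD and sample size behind it.

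Report the other spatial-temporal variables as mean differences with CIs. Treat SPM as exploratory, and say that the absence of a suprathreshold cluster is not evidence of equivalence.

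If no margin can be justified, remove the noninferiority label from the Study Design section and report estimates with CIs.

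The cost is a change of wording and one justified margin, with no new measurements. The power may prove less favourable than stated: if the justified margin is smaller than the effect used for the existing calculation, more participants would be needed for 90%.
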